### Clinical effectiveness

Linear mixed modelling will be used to examine whether changes in clinical effectiveness outcomes (ie, CAT, CETI, SAQOL-39, CCRSA), all of which are on interval scale, vary over time as well as across the two groups (usual care and CHAT), after adjusting for the effects of any potential confounders including linear trends over the usual care versus implementation phases. Before modelling the outcomes, baseline characteristics of the two groups will be examined, with any significant differences considered for modelling as covariates to adjust for their possible confounding effects. Collinearity of the covariates will be assessed before including them in the modelling. The results of the linear mixed models will be presented in the form of ORs and their 95% CI. Both intention-to-treat and per-protocol analyses will be conducted. Qualitative interview data will be analysed using thematic analysis.^50^

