### Sample size

The sample size calculations were conducted based on a secondary outcome measure of clinical effectiveness, due to the lack of existing data for the primary implementation outcome measure. We conducted a Monte Carlo power analysis using data from two sources: the Language Impairment and Functional Therapy trial (ACTRN12613001182785, n=17) and preliminary findings from the implementation of the CHAT programme at the Surgical Treatment and Rehabilitation Service study (ethics approval: HREC/2020/QRBW/50105, n=43). Model parameters were derived from a random intercept model of the effect of treatment on changes in CETI scores, with an estimated treatment effect of 9.08, a random intercept SD of 14.82 and a residual SD of 8.17. To simulate longitudinal data, each participant was assigned three repeated observations. Based on 1000 Monte Carlo iterations, a sample size of 55 participants per group (110 overall) was estimated to yield at least 80% power to detect the specified effect, assuming a two-tailed alpha of 0.05. With a projected attrition of 20%, a total of 138 participants overall (69 per group) is required.

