### Study status

Recruitment for the usual care period of the study was undertaken from April 2023 to February 2025. The intervention transition occurred across health services from August 2024 to June 2025. The CHAT implementation phase commenced in April 2025 and is ongoing.

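### The stated 80% power does not cover a clinical model whose linear trend competes with treatment, and a trend entered only as a main effect would leave a group-by-visit contrast unadjusted

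*Protocol article*

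**What the plan says.** Under Data analyses, Clinical effectiveness, the protocol article plans linear mixed models for four outcomes: CAT, CETI, SAQOL-39 and CCRSA. The models ask whether change varies over time and between the two groups "after adjusting for the effects of any potential confounders including linear trends over the usual care versus implementation phases". The article does not say whether the trend is a main effect or interacts with visit. The same paragraph adds: "Collinearity of the covariates will be assessed before including them in the modelling". It gives no threshold and no consequence.

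Under Sample size, the calculation rests on CETI: "Model parameters were derived from a random intercept model of the effect of treatment on changes in CETI scores". The inputs are an effect of 9.08 and SDs of 14.82 (between participants) and 8.17 (within participants). Each simulated participant has three observations, and the result is that "a sample size of 55 participants per group (110 overall) was estimated to yield at least 80% power to detect the specified effect". The test is two-sided at the 5% level. Allowing for 20% attrition gives 138 in total. No trend term is named.

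Under Study status: "Recruitment for the usual care period of the study was undertaken from April 2023 to February 2025". The CHAT phase began in April 2025 and is ongoing. Study periods plans that phase for years 3 and 4. The strengths and limitations box confirms that allocation is by time period.

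**The concern.** Every usual-care patient is enrolled before every CHAT patient, so a linear trend in enrolment date explains much of the same variation as the group indicator. The power figure comes from a model without that competitor, while the analysis is said to include it. Two outcomes are possible, depending on how the trend is entered:

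- If it acts on the treatment contrast, it adjusts for secular change but widens the standard error, so the 80% does not describe that analysis.
- If the effect is group-by-visit and the trend is only a main effect, precision is unchanged, but so is any bias from a drift in how much patients improve.

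CETI is a secondary outcome, but it is the only outcome with a power calculation and it sets the size of the study. In a non-randomised before-and-after design, the trend term is also the one named adjustment for secular change in the clinical models.

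**Working it through.** **Inputs from the article.** Effect 9.08, random intercept SD 14.82, residual SD 8.17, n = 55 per group, three observations, two-sided alpha 0.05 (Sample size); recruitment dates (Study status).

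**Assumptions.** Uniform accrual, complete visits, trend measured by enrolment month, and a CHAT phase of 12 to 24 months. Clustering by service is not modelled.

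**Step 1: reproduce the stated figure, without a trend.** Power = Φ(9.08/SE − 1.96), with SE = SD × √(2/55).

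- Total SD = √(14.82² + 8.17²) = 16.92. SE = 3.23 and power is 80.3%, which matches the stated 55 per group.
- Mean of three observations: SD = √(14.82² + 8.17²/3) = 15.55. SE = 2.97 and power is 86%.
- Baseline-to-post change (group-by-visit): SD = 8.17 × √2 = 11.55. SE = 2.203 and power is 98%.
- Attrition: 110/0.8 = 137.5, hence 138.

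**Step 2: overlap of period with calendar time.** Take windows of a and b months with gap g and equal groups. The difference in mean enrolment is D = a/2 + g + b/2. The average within-group variance is W = (a²/12 + b²/12)/2. The variance inflation factor is VIF = 1 + (D/2)²/W, and r² = 1 − 1/VIF.

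- a = 23, g = 1, b = 23: D = 24, W = 44.08, VIF = 1 + 144/44.08 = 4.27, r = 0.875.
- a = 23, g = 1, b = 12: D = 18.5, W = 28.04, VIF = 1 + 85.56/28.04 = 4.05, r = 0.868.
- Counting usual care as 22 months with a 2-month gap, b = 12 to 24: VIF = 4.45 to 4.59, r = 0.880 to 0.884.

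**Step 3: power when the trend acts on the treatment contrast.** SE is multiplied by √VIF, that is by 2.01 to 2.14.

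| Contrast | Power, no trend | Power, VIF 4.05 to 4.59 |
|---|---|---|
| Level, total SD | 80% | 26 to 29% |
| Level, mean of three | 86% | 30 to 33% |
| Group-by-visit, with trend-by-visit | 98% | 49 to 54% |

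Worked example at VIF 4.27, change contrast: SE = 2.203 × 2.066 = 4.55; 9.08/4.55 − 1.96 = 0.035; power 51%. Exact generalised least squares for the three-visit random intercept model gives the same SE, 4.552. Separate slopes in each phase, with the effect read at the start of CHAT, give 4.555.

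With the 23-month usual-care window and 1-month gap, 80% power would need about 103 to 233 per group, depending on the contrast. If all 69 per group were retained, simulated power would be about 33 to 62%.

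**Step 4: trend as a main effect only, effect group-by-visit.** The SE is 2.203 with the trend and 2.203 without it. As an illustration, let improvement drift by 0.1 CETI points per calendar month. With mean enrolment 24 months apart, the contrast is biased by 0.1 × 24 = 2.4 points, with or without the main-effect trend. With trend-by-visit, the bias is 0.

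**Step 5: sensitivity to the gap.** Study status dates the transition across services from August 2024 to June 2025, so gaps within a service may be longer. Illustratively, VIF is 5.2 for a 4-month gap (a = 23, b = 21) and 7.0 for an 8-month gap (a = 17, b = 21).

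**The case against.** The strongest reply is that a journal article need not give the functional form of a covariate, and that powering on an unadjusted effect is ordinary practice. Both points stand in part: silence on the form is not itself the defect. But the article does state a trend adjustment and a power figure. In no form where the trend truly adjusts the treatment contrast does the figure hold at 55 per group.

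Four stronger readings are tempting and are not supported:

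- **Period and time are so collinear that the effect cannot be estimated.** A correlation of 0.87 to 0.88 leaves it estimable, though only through linear extrapolation.
- **The trend adjusts nothing.** This is true only for a main-effect trend in a group-by-visit model with complete visits. If treatment is a group effect on level or on change scores, a main-effect trend does adjust it and costs the power. The article's wording fits either.
- **The collinearity check will remove the trend.** The article says only that collinearity of covariates is assessed. It does not say that the trend is tested against group, or that a flagged term is dropped.
- **The trend should leave the main model to protect the 80%.** In a non-randomised design this is a debatable trade-off, and nothing in the article requires it.

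It also stands that CETI is secondary and that the primary composite's analysis is not affected by this point.

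**Conclusion.** The concern holds in conditional form. The 80% applies to a model without a trend. Once the trend competes with treatment, power at 55 per group is about 26 to 33% for an effect on level or 49 to 54% for a group-by-visit contrast. The alternative, a main-effect trend beside a group-by-visit effect, keeps the power but leaves that contrast open to drift in improvement. The two consequences belong to different models and cannot both apply to one.

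The figures rest on uniform accrual, the assumed CHAT phase length, enrolment month as the time scale, and no clustering by service. They change little between 12 and 24 months and worsen with longer gaps.

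**What to change.** - Specify the trend, using recruitment date, so that it acts on the treatment contrast: trend-by-visit if the effect is group-by-visit.
- State that the trend is kept whatever the collinearity check shows.
- State under Sample size that the 80% applies only to the model without a trend. Give the power or expected interval width for the model with it. For the change contrast at VIF 4.27, for example, the 95% half-width goes from 1.96 × 2.203 = 4.3 to 1.96 × 4.552 = 8.9 CETI points.
- Fix in advance whether the trend-adjusted model is the main analysis or a pre-specified sensitivity analysis, and report both estimates. That choice is the sponsor's.

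This takes wording and a short rerun of the simulation, with no new data. CHAT is still running, so it can be settled now. The downside is a visibly less favourable power for the trend-adjusted analysis.

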**Registration details:**

Australian New Zealand Clinical Trials Registry (ANZCTR) prospective registration ACTRN12621001765819. Trial registered 23 December 2021. https://anzctr.org.au/Trial/Registration/TrialReview.aspx?id=381365&isReview=true.

STRENGTHS AND LIMITATIONS OF THIS STUDYA hybrid implementation-effectiveness study design will support a rapid research translation and uptake of the Comprehensive High-dose Aphasia Treatment (CHAT) programme at trial completion by identifying effective implementation strategies that can be tailored to local barriers, and provide concurrent answers about intervention effectiveness in real-world settings.This study will be conducted across six Australian hospitals and health services, to compare the effectiveness and cost-effectiveness of usual care with the CHAT programme, which has been developed to address known aphasia rehabilitation evidence-practice gaps.A diversity of health services will be involved in this study (ie, metropolitan, regional, hospital-based and community-based services), which will allow us to examine implementation in different settings.This study only includes people with post-stroke aphasia who speak English, therefore limiting generalisability to other aetiologies and patients from other linguistic backgrounds.Due to the non-randomised, pre-post design with the allocation of people with aphasia based on time periods, various risks of bias are possible, including selection bias.

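### Baseline confounders for the clinical effectiveness models are screened by significance test, which at 55 to 69 per group usually misses imbalances below about 0.33 to 0.37 SD

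*Protocol article*

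**What the plan says.** All of this is in the protocol article; the statistical analysis plan is not shown.

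- **Adjustment in general** (Data analyses, Clinical effectiveness). The linear mixed models for CAT, CETI, SAQOL-39 and CCRSA compare change over time between usual care and CHAT, "after adjusting for the effects of any potential confounders including linear trends over the usual care versus implementation phases". The linear trend is the only adjuster named.
- **Baseline characteristics** (same paragraph). The two groups are compared first, "with any significant differences considered for modelling as covariates to adjust for their possible confounding effects". A collinearity check follows. The level of the baseline tests is not stated.
- **Design** (Strengths and limitations). "Due to the non-randomised, pre-post design with the allocation of people with aphasia based on time periods, various risks of bias are possible, including selection" bias.
- **Size** (Sample size). "a sample size of 55 participants per group (110 overall) was estimated to yield at least 80% power to detect the specified effect", inflated to 69 per group for 20% attrition.

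**The concern.** Confounding by a baseline factor is the product of two things: how far the groups differ on it, and how strongly it predicts the outcome being contrasted. A significance test of the baseline difference measures neither cleanly. It mixes the size of the difference with the sample size, and it takes no account of prognostic strength. A strongly prognostic factor with a moderate imbalance can be dropped, while an irrelevant factor with a large chance imbalance is kept.

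In a randomised trial this would matter less. Here calendar period sets the group, treating clinicians and site champions identify the patients, the services span inpatient, outpatient and community care, and the listed eligibility criteria set no limit on time since stroke. A real shift in case mix between periods is plausible, and covariate adjustment is the main analytic protection the article states against it. At stake is the clinical comparison of CHAT with usual care, the study's second aim.

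**Working it through.** **1. The plan's own sample size.** Inputs from Sample size: "with an estimated treatment effect of 9.08, a random intercept SD of 14.82 and a residual SD of 8.17", two-sided alpha 0.05, power 80%.

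- Total SD = √(14.82² + 8.17²) = √(219.63 + 66.75) = 16.92.
- n per group = 2 × (1.96 + 0.8416)² × 16.92² / 9.08² = 54.5, so 55 (power 80.3%).
- Attrition: 55/0.8 = 68.75, so 69; 110/0.8 = 137.5, so 138.

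The stated figures reproduce. The checks below use 55 (evaluable) and 69 (enrolled) per group.

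**2. What the screen can see.** Assumed: baseline tests at two-sided 0.05. The standard error of a standardised mean difference is √(2/n), which is 0.191 at 55 and 0.170 at 69. A difference is flagged only if the observed value exceeds 1.96 × 0.191 = 0.37 SD, or 1.96 × 0.170 = 0.33 SD. For a true imbalance s, the chance of missing it is Φ(1.96 − s/SE) − Φ(−1.96 − s/SE):

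| True imbalance (SD) | Missed, 55 per group | Missed, 69 per group |
|---|---|---|
| 0.1 | 92% | 91% |
| 0.2 | 82% | 78% |
| 0.3 | 65% | 58% |
| 0.4 | 45% | 35% |
| 0.5 | 25% | 16% |

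**3. Mean bias left by one confounder.** Simulation with 55 per group, outcome SD 16.92, no treatment effect, 5000 runs. The confounder's correlation with the modelled outcome is assumed to be 0.3 to 0.5. Bias is in CETI points:

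| Imbalance (SD) | Unadjusted | Screened | Always adjusted | Share left by screening |
|---|---|---|---|---|
| 0.2 | 1.05 to 1.72 | 0.58 to 1.00 | about 0 | 55-58% |
| 0.3 | 1.50 to 2.53 | 0.60 to 1.06 | about 0 | 40-42% |
| 0.4 | 2.10 to 3.34 | 0.60 to 0.88 | about 0 | 26-29% |
| 0.5 | 2.52 to 4.32 | 0.32 to 0.63 | about 0 | 13-15% |

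The largest screened value is 1.06/9.08 = 12% of the planned effect. With a single confounder the screened analysis rejected in about 5% of runs (4.7% to 5.9%).

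**4. Several confounders and a change contrast.** The article models change, so a factor that shifts only the level of a score cancels. Simulation of baseline-to-post change, 55 per group, no treatment effect, 6000 runs. Four independent confounders are each imbalanced by 0.25 SD in the same direction. Change SD = √2 × 8.17 = 11.55. Each confounder predicts change with coefficient c, in units of that SD. The two figures in a cell treat 11.55 as the residual and as the total SD of change.

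| c | Rejection, screened | Rejection, all four adjusted | Bias left by screening (CETI points) |
|---|---|---|---|
| 0 (level only) | 4.6% / 5.5% | 5.0% / 5.6% | about 0 |
| 0.1 | 5.6% / 6.0% | 4.6% / 5.3% | 0.56 / 0.60 |
| 0.2 | 7.2% / 7.8% | 5.2% / 5.4% | 1.17 / 1.13 |
| 0.35 | 11.1% / 14.2% | 5.1% / 4.5% | 2.07 / 2.07 |

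At c = 0 the selection is unrelated to the outcome, so the true rate is the nominal 5% and the spread is simulation error. The screen picks about 1 of the 4 confounders. At c = 0.35 the unadjusted bias is 4 × 0.25 × 0.35 × 11.55 = 4.04 points, so about half remains.

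**The case against.** Five arguments can be made for the plan.

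- **The text is wider than the screen.** The models adjust for potential confounders in general, the linear trend is not tied to a test, and an unseen analysis plan may list covariates. This stands in part: it would be wrong to say that nothing enters without a significant test. But the general phrase names no baseline variable and the next sentence supplies the method. The fault is in the rule stated, not in an omission.
- **A change contrast removes stable level differences.** This stands. A factor such as severity or age biases the result only if it also predicts change.
- **The screen does help.** This stands. Imbalances of 0.4 SD or more are found more often than missed, and from 0.3 SD upward less than half of one confounder's mean bias remains. A reader might infer that most real imbalance would go unadjusted; the calculation supports that only for imbalances below about 0.33-0.37 SD.
- **A large rise in false positives is a worst case.** A reader might quote 14% as the error rate of this trial. The documents do not support that. It needs four confounders in the same direction, each with coefficient 0.35, together explaining about half of the variance (4 × 0.35² = 0.49). In a single-outcome version of that scenario, reversing one confounder gives about 6%, and balancing two against two gives no inflation.
- **Selection bias is admitted.** It is, as one of various risks; the article does not rank it as the main one. Admitting it does not repair a weak adjustment rule.

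**Conclusion.** The point holds for baseline characteristics in the clinical effectiveness models. The stated rule selects confounders on the wrong criterion, and at 55 to 69 per group it usually passes over imbalances below about 0.33-0.37 SD. The detection figures depend only on the sample size and an assumed 0.05 level. The bias figures (40-58% of one confounder's mean bias kept at 0.2-0.3 SD, at most about 1.1 CETI points) also assume a correlation of 0.3 to 0.5 with the modelled contrast. The false-positive effect cannot be fixed from the document: about 5% to about 14% in the four-confounder change scenario, depending on how strongly those factors predict change.

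A reader might extend this to the primary outcome, the composite of quality indicators analysed by median regression. Nothing here shows that: it is a process-of-care score with a different model, and none of the calculations address it. The change is advisable rather than essential, because the outcomes concerned are secondary.

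**What to change.** Delete the significance screen from the clinical effectiveness paragraph. Name a short adjustment set chosen on prognostic grounds from recorded data, for example age, baseline CAT severity, care setting, service, and time since stroke if it is recorded. Include all of it whatever the baseline p-values.

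Three details need care.

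- **Interactions.** Where a factor may predict change, enter it with its interaction with time. With complete data, a main effect alone leaves the group-by-time contrast unchanged.
- **The outcome's own baseline.** Treat it either as one of the repeated outcomes or as a covariate, not both. This applies to CAT severity in the CAT model.
- **Availability.** The article does not list time since stroke as collected. Table 3 places patient demographics in a log footnoted to period 3 only. Confirm that each chosen covariate exists for both periods.

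Cost: wording, and roughly 10 degrees of freedom for main effects if service is a fixed factor (six services 5, three care settings 2, age 1, CAT 1, time since stroke 1). It is fewer if service is a random effect, and time interactions add to it. The sample size and visits do not change. The article reports the CHAT phase as ongoing, so the change can be made before the two periods are compared.

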## Data analyses

### Implementation effectiveness

Median regression will be used to compare differences between usual care and CHAT implementation periods for the primary outcome measure, overall composite score: proportion of quality indicators received. The model will be adjusted for patient clustering by service, to protect against residual confounding. Multilevel logistic regression analysis, with levels defined as patients and hospital, to adjust for patient clustering, will be used for dichotomised outcomes such as those relating to individual quality indicators.

Programme reach and quantitative survey data will be analysed using descriptive statistics (eg, m, SD, IQR). For continuous survey data, mean within-group differences will be calculated using paired t-tests and 95% CI. Qualitative data will be analysed using content analysis^49^ and guided by a theoretically grounded approach to analysis of barriers and facilitators to implementation (eg, Theoretical Domains Framework). Comparative analysis will occur between sources (eg, participants, speech pathologists, allied health assistants) to identify common and distinctive themes.

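### The four quantitative clinical outcomes are to be reported as odds ratios from linear mixed models, which estimate mean differences in score points instead

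*Protocol article*

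**What the plan says.** Under Data analyses, Clinical effectiveness, the protocol article assigns CAT, CETI, SAQOL-39 and CCRSA to linear mixed modelling. It describes the four scales as "all of which are on interval scale". The question is whether change over time differs between usual care and CHAT, after adjustment for confounders. The same paragraph then fixes the effect measure: "The results of the linear mixed models will be presented in the form of ORs and their 95% CI".

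Two other sections bear on this.

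- **Sample size.** The planning values come from a model of the same kind: "Model parameters were derived from a random intercept model of the effect of treatment on changes in CETI scores". The effect taken from it is 9.08, and the two SDs are 14.82 (between participants) and 8.17 (residual).
- **Data analyses, Implementation effectiveness.** This section holds the only logistic model in the article, a multilevel logistic regression that "will be used for dichotomised outcomes such as those relating to individual quality indicators". It does not name an effect measure.

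**The concern.** A linear mixed model has an identity link. Its fixed effects are differences in the mean of the outcome, in the units of the outcome. The group-by-time term answers the question the article poses: by how many points does mean change differ between CHAT and usual care? No odds are modelled, so no odds ratio comes out.

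At stake is the prespecified effect measure for every quantitative outcome in the comparison of clinical effectiveness. An analyst who tried to follow the sentence would have to exponentiate a coefficient that is not a log odds, or add a step that the article does not describe. An analyst who ignored it and reported mean differences would be right, but would depart from the published plan. In a non-randomised study whose participants and assessors are not blinded, such a departure should not happen without a record.

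**Working it through.** **1. Could the sentence refer to another model?** It names the linear mixed models and stands in the paragraph that defines them. The logistic models are under a different heading and serve dichotomised outcomes, with the individual quality indicators as the example. The article nowhere plans to split the four scales at a cut-point, model them ordinally, or convert a standardised difference to an odds ratio.

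**2. What scale does the planning effect use?** The Sample size section does not write a unit next to 9.08, so I checked whether it behaves as a difference in CETI points.

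Inputs, all from Sample size: effect 9.08, random intercept SD 14.82, residual SD 8.17, two-sided alpha 0.05, power 80%, attrition 20%.

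- Total SD of one observation = √(14.82² + 8.17²) = √(219.63 + 66.75) = √286.38 = 16.92.
- n per group = 2 × (1.960 + 0.842)² × 286.38 / 9.08² = 2 × 7.85 × 286.38 / 82.45 = 54.5, rounded up to **55**. The article also gives 55. Power at 55 is 0.803 (normal approximation).
- Attrition: 110 / 0.80 = 137.5, rounded up to **138**; 55 / 0.80 = 68.75, rounded up to **69**. Both match the article.

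So 9.08 works as a mean difference in the same units as the two SDs. (Averaging the three simulated observations per participant would give an SD of 15.55 and need 47 per group. That does not affect this point, and the claim of at least 80% power still holds.)

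**3. What does the stated model return?** One data set was simulated with these parameters: 55 per group, three observations each, and the effect placed after baseline. A linear mixed model gave a group-by-post coefficient of 8.40 (95% CI 5.16 to 11.63). This is a difference in mean change, in points.

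**4. Does exponentiating help?** exp(9.08) is about 8,778. If the same score is divided by 100, the same effect becomes exp(0.0908), about 1.10. A true odds ratio for an outcome would not change with the unit of the score, so the exponentiated coefficient is not one. These two numbers only illustrate that; the article does not propose exponentiation and they do not measure the size of the error.

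**The case against.** The strongest reply is that this is a slip in how secondary results are presented. The primary outcome is the composite of quality indicators, analysed by median regression. The model, data, covariates and sample size for the clinical scales stay as they are. The software will print coefficients in scale points, so the slip would probably surface at the first model fit. All of this stands and limits the damage. It does not make the sentence right, and nothing else in the article corrects it.

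A reader might be tempted by stronger conclusions that the document does not support:

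- **That no odds ratio could exist for such outcomes without dichotomising.** This is too absolute. A cumulative ordinal model yields odds ratios, and a standardised difference can be converted approximately: 9.08 / 16.92 = 0.54, and exp(0.54 × π/√3) is about 2.6 under a logistic assumption. The supportable claim is narrower: the stated model does not estimate an odds ratio, and the article plans no such route.
- **That the cost-effectiveness analysis is blocked.** Economic evaluation does not say that it takes its effects from these reported estimates. It names patient-level data among its sources, and the scores remain available.
- **That all of the clinical effectiveness aim is lost.** That aim also has a qualitative part, with interviews analysed thematically.
- **That information is lost as by a median split.** The article does not plan such a split, so no loss of this kind can be charged to it.

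**Conclusion.** The sentence is wrong as written. It prespecifies an effect measure that its own model does not produce, and it conflicts with the points-scale CETI effect of 9.08 used for sample size. This is a positive statement in the article, not a detail left to an analysis plan.

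The error covers the reported effect measure for four secondary outcomes: CAT, CETI, SAQOL-39 and CCRSA. The primary outcome, the sample size (55 per group, 138 in total after attrition) and the power are unaffected. No numerical bias can be attached to it, because the article describes no calculation that would lead to an odds ratio.

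The conclusion rests on two readings: that linear mixed model has its usual meaning (identity link, continuous outcome), and that 9.08 is in CETI points. The interval-scale description supports the first, and the reproduction of 55 per group supports the second.

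**What to change.** Replace the sentence with one saying that results of the linear mixed models will be presented as adjusted between-group mean differences in change (the group-by-time contrasts), in scale points, with 95% CI. If odds ratios are wanted anywhere, they suit only the multilevel logistic models of dichotomised outcomes under Implementation effectiveness, where the effect measure could be named.

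The cost is one sentence. No data collection, sample size or model changes. Study status says that the CHAT phase is ongoing, so the correction can be put on record before the final analysis. If it is handled as a protocol amendment, the only further step is the ethics and governance approval that the article already foresees for amendments.
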